**Fig. 3 Fig3:**
[figure not shown]
Map of Say Yes! COVID Test intervention counties and the five groups of matched controls communities for each state, comprising the best matches for each of the following categories of matching variables: demographics (including age distribution and racial and ethnic diversity), mobility, population density, risk factors/comorbidities, socioeconomic status (including per capita income), and incidence/vaccination trajectory

We also selected multiple matched control communities for each intervention community within the same state to control state-level trends and policies **(**Fig. 3**)**. Given the limited number of counties in each state and potential confounders, no single community or composite of communities was likely to be identified as a good match in every factor affecting the outcomes. Instead, we selected five groups of matched controls for each state, comprising the best matches for each of the following categories of matching variables: demographics (including age distribution and racial and ethnic diversity), mobility, population density, risk factors/comorbidities, socioeconomic status (including per capita income), and incidence/vaccination trajectory. We chose most of the matching categories and individual variables to mirror as much as possible the National Institute of Environmental Health Sciences COVID-19 Pandemic Vulnerability Index [19]. To select control communities for the wastewater analyses, we used wastewater data availability, comparability of the sewer shed, and consistency of lab procedures as criteria.

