##### Sample size and power calculation:

We did not perform a formal power calculation since this is an ecological study. We anticipate that approximately 40,000 households in each intervention community (NC and TN) will participate based on test kit availability. Due to the limited number of intervention communities and only observing outcomes at the community level, there is insufficient power to conduct formal hypothesis tests about the effect of the intervention. Therefore, the proposed analysis is strictly descriptive rather than inferential.

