We will use mixed modeling techniques to compare trends over time between intervention and control communities. Specifically, for each outcome and intervention/control community matched pair, a generalized linear model of 7-day average or twice-weekly outcomes by community and time with a time-by-community interaction will be fit, adjusted for vaccination coverage and the percentage of SARS-CoV-2 cases attributable to the B1.1.7 variant. Correlated residuals will be modeled within a community with an autoregressive correlation structure. The community will be modeled with a categorical fixed effect. Time will be modeled using restricted cubic splines. Four knots will be considered: at the beginning, at the transition from one period to the next, and at the end. Piecewise linear splines by period will also be considered for adequate fit. Linear time-by-community interactions will be included for each time. Vaccination coverage and percent of SARS-CoV-2 cases attributable to the B1.1.7 variant (estimated from wastewater data) will be modeled as a time-varying covariate where available, transformed as needed. The appropriate distribution and respective canonical link function will be used for each outcome type on the multiplicative/log scale when possible—i.e., binomial if a proportion, Poisson if discrete, log-transformed, and normal if continuous. Each intervention community will be compared to each matched control community separately within the intervention periods. This will be done by comparing the appropriate time-by-community interaction parameters using a likelihood ratio test with alpha = 0.05. This analysis will be repeated for the wastewater viral concentrations data.

Trends in mobility outcomes should be interpreted with caution. The outcome will reflect trends on the day of the week not corrected by the baseline value. The analytic team will consider smoothing methods to mitigate this effect.

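### The ecological analysis is declared strictly descriptive, yet it prescribes pairwise likelihood ratio tests at alpha = 0.05 that can show only that two counties' trends differ

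*Protocol article*

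**What the plan says.** All places are in the protocol article.

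- **Sample size and power calculation (ecological analysis).** Because there are few intervention communities and outcomes are seen only at community level, "there is insufficient power to conduct formal hypothesis tests about the effect of the intervention". The section concludes that "the proposed analysis is strictly descriptive rather than inferential". The Discussion repeats this more softly, calling the analysis primarily descriptive.
- **Analysis plan, unit of modelling.** The plan is to fit, "for each outcome and intervention/control community matched pair, a generalized linear model of 7-day average or twice-weekly outcomes by community and time". The model lets the time trend differ between the two communities and adjusts for vaccination coverage and B1.1.7 share.
- **Analysis plan, error structure.** "The community will be modeled with a categorical fixed effect". Residuals are autoregressive within a community.
- **Analysis plan, comparison and decision rule.** "Each intervention community will be compared to each matched control community separately within the intervention periods". The decision rule comes next in that section: "This will be done by comparing the appropriate time-by-community interaction parameters using a likelihood ratio test with alpha = 0.05". Nothing in that section labels these tests exploratory.
- **Study sites.** There is one intervention community in North Carolina and one in Tennessee. For controls, "we selected five groups of matched controls for each state". The same paragraph concedes that no single or composite control was likely to match on every relevant factor.

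**The concern.** Two things are wrong. First, one section rules out formal tests of the intervention and another prescribes one for every outcome and every pair. A later analysis plan could not follow both.

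Second, the prescribed test treats days as the replicates. With one county on each side, it asks whether two curves differ by more than day-to-day noise allows. It does not ask whether they differ by more than two untreated counties would. The Background says the aim is to find out whether home testing lowers community transmission. A p-value below 0.05 for the primary outcome would invite that conclusion, for benefit or for harm, when the cause could be ordinary divergence between imperfectly matched counties. The article gives low power as its reason for caution. With this test, false positives are at least as serious a risk.

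**Working it through.** **1. The plan's own figure.** The only figure is alpha = 0.05 per comparison. For a 1-df likelihood ratio test the cutoff is 1.96² = 3.84. No power or sample size figure is stated for this analysis, so there is nothing else to reproduce.

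**2. What the test measures.** In one pair, let δ be the intervention effect on the trend. Let u₁ and u₀ be the two counties' own departures from the shared trend, each with variance τ². The fitted interaction estimates

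δ + (u₁ − u₀), with true variance v + 2τ²,

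where v is the sampling variance from the within-county residuals. The model reports only v. With δ = 0 the rejection probability is

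P(|Z| > 1.96 × √[v / (v + 2τ²)]).

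If τ = 0 this is 0.05. If 2τ² = v it is P(|Z| > 1.96/√2) = P(|Z| > 1.386) ≈ 0.17. More days of data shrink v but leave τ² unchanged, so a longer series makes the problem worse. One county per arm cannot supply an estimate of τ², whether or not the model is called mixed. Autoregressive residuals absorb short-term wandering but not a sustained difference in trend.

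**3. Length of series.** In Pitt County the pre-intervention period runs from January 1 to the day before April 4, 2021: 31 + 28 + 31 + 3 = 93 days. The intervention period is 11–12 weeks (81 days used) and the post-intervention period is 90 days, giving 93 + 81 + 90 = 264 days. Hamilton County began on May 4, so its series is about a month longer.

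**4. Simulated rejection rates with no intervention effect.** Counts were overdispersed and daily. The model used the log of the 7-day average, a fixed community effect, piecewise-linear time by period and AR(1) residuals, with 400 runs per setting. All divergence settings are assumptions, because the documents give none.

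| Assumed divergence between counties | Null rejection, 1-df test |
|---|---|
| None (30 or 100 cases/day) | 2.5%, 2.25% |
| Temporary drift in log incidence, SD 0.2, correlation time 14 days | 8.8% |
| SD 0.3, 21 days | 11.5% |
| SD 0.3, 28 days | 17% |
| SD 0.4, 42 days | 20.5% |
| Random walk, SD 0.05 / 0.10 / 0.20 per week (50 cases/day) | 18% / 40% / 40% |
| County slope SD 0.03 per week (30 or 100 cases/day) | 43%, 54% |
| County slope SD 0.05 per week | 61%, 71% |
| County slope SD 0.10 per week | 76%, 84% |

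The temporary-drift rows used 263 days and 25 to 60 cases per day, and tested the interaction at the start-of-intervention knot. The other rows used 264 days and tested the slope difference during the intervention period. That is one reason the two sets differ.

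**5. A yardstick for the assumptions.** The intervention period is 81/7 = 11.57 weeks. With a slope SD of 0.03 per week, the gap opening between two counties has SD √2 × 0.03 × 11.57 = 0.49 on the log scale, a factor of e^0.49 ≈ 1.6. With SD 0.10 it is √2 × 0.10 × 11.57 = 1.64, a factor of about 5.1, which is extreme. With a random walk of 0.05 per week it is 0.05 × √(2 × 11.57) = 0.24, a factor of about 1.3.

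**6. What one state can support.** If the county is the unit and the intervention county is ranked among J controls, the smallest attainable p is 1/(J + 1). With five control units, assuming one per group, this is 1/6 = 0.167. One state with five controls cannot reach 0.05 on this basis.

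**The case against.** The strongest reply is that the article already discloses the limitation. It cites the small number of intervention communities and community-level observation, which is the replication problem, and it tells readers twice that the work is descriptive. Controls come from the same state, and the models adjust for vaccination and variant share. Several imperfect controls were chosen deliberately, so disagreement among them is informative. This stands as mitigation. It does not explain why a test with a fixed alpha is prescribed, and the adjustments (time-varying only where data exist) remove only part of the divergence.

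The reply is also right that the simulations simplify the plan. They omit the covariate adjustment, use piecewise-linear time where restricted cubic splines are named first, use a log-normal model where Poisson is named for counts, and take autoregressive to mean first order. The rates are illustrations, not predictions for this study.

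Three stronger readings are tempting, and the documents do not support them:

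- *That the programme will declare a significant interaction to be an intervention effect.* No section says so. The Analysis plan speaks of comparing trends.
- *That about 60 tests are planned (2 states × 5 groups × 6 outcome rows), giving 60 × 0.05 = 3 false positives.* The article does not state how many communities each group holds. Wastewater controls were chosen by other criteria, the mobility row covers several measures, and two more communities are to be added. The count cannot be derived.
- *That the lack of a multiplicity rule is a defect.* That may be left to an analysis plan that is not shown.

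**Conclusion.** The contradiction between the sample size section and the Analysis plan is explicit and needs no assumption. That the pairwise test cannot separate the intervention from county divergence follows from the stated model: one county per arm, a fixed community effect and residual correlation only within county. It too needs no outside figure.

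The size of the false-positive problem does rest on assumptions. Over the divergence settings tried, a single null pair is rejected in roughly 9% to over 40% of cases, reaching 84% in the most divergent setting. Without divergence the rate is 2% to 3%, so in these simulations the excess comes from the divergence and not from the fitting method. Because the article concedes imperfect matching, zero divergence is not a safe assumption. The point matters because this is the only comparative analysis specified for the primary outcome.

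**What to change.** 1. In the Analysis plan, delete the likelihood ratio test at alpha = 0.05, so that the section agrees with the descriptive status declared under Sample size and power calculation.
2. Report each intervention-period trend contrast with its size. State beside any model-based interval that it does not include between-county variation in trend.
3. Preferably, add a placebo comparison. Refit the same contrast treating each matched control county in turn as the intervention county, with that state's start date, and show where the true intervention county ranks. State the attainable floor of 1/(J + 1), for example 1/6 with five control units. Other ways of displaying untreated divergence would also serve. A single pooled contrast per state is not required, given the article's reason for avoiding a composite control.
4. As a minor and separate correction under Study sites and in the Fig. 3 legend, reconcile the five announced control groups with the six matching categories listed.

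The cost is a wording change and, for item 3, a loop over control counties whose data are already being collected. The price is that no conventional p < 0.05 statement will be available.

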### Behavioral substudy

#### Study population

Adults and children > 8 years of age living within the two communities currently participating in the public health intervention were eligible for the substudy.

#### Study questionnaires

Those who provide consent and enroll in the substudy are asked to complete questionnaires through an app and report any positive test results. Participants complete surveys and questionnaires through the smartphone app or via the call center according to the schedule of events (Additional file 3)**.** Questionnaires collect data on demographic characteristics, medical history, and health status; SARS-CoV-2 at-home testing and symptoms and any additional PCR testing obtained in response to symptoms; social interactions; knowledge of prevention strategies; infection risk; and attitudes toward vaccines. Questionnaires are completed during the week after each test (regardless of the result). We did not track participant-reported deviations to the recommended SYCT testing protocol.

#### Questionnaire distribution

The MyDataHelps smartphone application developed by CareEvolution (see ‘SYCT Intervention and Ecological Analysis’ section above) is also being used for the SYCT behavioral substudy [20]. Once registered, if the participant elects to be a part of the substudy, eligibility criteria are verified, and e-consent is obtained through the app. Push notifications are programmed with text messaging to promote adherence, including personalization, context, and timing for all participants in the public health intervention. Additionally, participants can opt-in to reminders for testing three times a week at a time of their preference. For participants who provided consent to the substudy, the app also features the ability to report their test results (upload images of test trips), track testing history, respond to surveys and questionnaires, and access the study team’s contact information.

Alternatively, participants who choose not to use the app can provide their information via phone interviews conducted by a centralized study call center. Using scripted interview guides, call center staff members explain study participation, obtain verbal consent, administer study questionnaires including soliciting test results, and issue phone reminders.

#### Statistical considerations and data analysis

##### Outcomes and measures:

The substudy hypothesis is that positive at-home test results will be associated with altered self-reported social interactions and altered health behaviors compared to negative test results. Our outcomes of interest for the substudy are the behavioral determinants of testing (social interaction, health behaviors, healthcare utilization, prevention knowledge, and vaccine attitudes). All outcome measures will be self-reported through the study questionnaires on an individual level. The frequency of measurement is described in Additional file 3**.** Outcome measures and endpoints are outlined in Table 3**.**

**Table 3 Tab3:** Primary and secondary outcome measures and endpoints for the SYCT substudy

Outcome Measures	Endpoint
**Primary**	
Self-reported data on social distancing, quarantine, social connectedness, healthcare utilization, well-being	The proportion of respondents who report adhering to social distancing guidelines after a test result for the entire study cohort and stratified by participant demographics (e.g., gender) of interest; comparison of proportion adherent after positive vs. negative test result

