#### Testing protocol

Each participating household received one kit of 25 tests each. All test kits included an informational brochure with clear written instructions with visual aids and links to videos in English and Spanish. We instructed the participants to test one or two asymptomatic individuals within the household three times per week until all tests were used (4–5 weeks; Fig. 6). We encouraged participants to prioritize household members with the highest risk of exposure to or infection with SARS-CoV-2, such as those who worked outside the home, were not vaccinated for SARS-CoV-2, or had not been previously infected. If an individual tested positive by rapid test, we instructed them to stop testing and give their remaining tests to another household member. The SYCT program did not require positive antigen test results reporting, although, for TN participants, a phone number was available for voluntary reporting.

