**Fig. 6 Fig6:**
[figure not shown]
At-home testing protocol for Say Yes! COVID Test intervention

If a participant developed any symptoms consistent with COVID-19 disease (e.g., fever, cough, shortness of breath), we recommended that the participant contact their primary physician or the local health department to obtain a PCR test for SARS-CoV-2. Reporting positive results to the health department was done through the testing institution; SYCT did not mandate result reporting. At the time of symptoms, we did not recommend additional at-home testing outside of the thrice-weekly schedule.

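### The substudy's comparison of behaviour after a positive versus a negative home test takes no account of symptoms at the test, so it cannot support the causal wording of its hypothesis

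*Protocol article*

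**What the plan says.** **Who tests.** The Testing protocol section states: "We instructed the participants to test one or two asymptomatic individuals within the household three times per week until all tests were used". It gives one reason for an individual to stop: "If an individual tested positive by rapid test, we instructed them to stop testing". For a participant who develops symptoms, the text under Fig. 6 advises them to "contact their primary physician or the local health department to obtain a PCR test for SARS-CoV-2" and adds: "At the time of symptoms, we did not recommend additional at-home testing outside of the thrice-weekly schedule". It does not say whether the scheduled tests go on or cease.

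**Who is in the substudy.** Adults and children above the age limit "living within the two communities currently participating in the public health intervention were eligible for the substudy". No symptom criterion is given.

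**What is recorded.** Under Study questionnaires, participants answer in the week following every test, positive or negative. The items include symptoms and any PCR test prompted by them. The same section says: "We did not track participant-reported deviations to the recommended SYCT testing protocol".

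**What is compared.** Table 3 gives as part of the primary endpoint the "comparison of proportion adherent after positive vs. negative test result". The primary outcome measures in that row also include quarantine and healthcare utilization. The substudy's Data analysis plan explores associations between positive results and behaviour with mixed models, whose stated purpose is to allow for correlation within participants and households. It calls the analysis primarily descriptive, yet words its exploratory hypothesis as positive results causing changed behaviour. The substudy's Outcomes and measures section words the same hypothesis as an association.

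**The concern.** Symptoms meet the usual conditions for a confounder of this contrast. They can be present before the result is read, they make a positive antigen result more likely, and they lead people to stay at home and seek care whatever the strip shows. The article's own advice adds to this, because a symptomatic participant is told to contact a physician or health department. Contact with health services is thus prompted by symptoms, while healthcare utilization is among the primary outcome measures.

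If positive tests are more often symptomatic than negative ones, a crude comparison credits the test result with behaviour that the symptoms produced. A random effect for participant or household does not remove this, since symptoms vary from one test to the next within the same person. What is at stake is the reading of the substudy's main finding: a sizeable difference could appear even if learning the result changed nothing.

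**Working it through.** The article states no figure for this contrast, so there is none to reproduce. The only substudy precision figure is a 1.5% margin at 50% adherence with 5000 participants. The half-width is 1.96 × √(0.25/5000) = 1.39%, so that statement holds. It describes random error in one overall proportion and does not bear on bias in the contrast.

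**Step 1: can tests taken with symptoms enter?** The following texts are set side by side.
- The instruction names asymptomatic people as those to test.
- The only individual stop rule is a positive result.
- On symptoms, the advice is against tests outside the thrice-weekly schedule; nothing suspends the schedule.
- Substudy eligibility has no symptom criterion, and a questionnaire follows every test.
- Deviations from the testing protocol are not tracked.

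Together these leave a route for symptomatic tests into the data. That is inferred; no sentence tells symptomatic people to go on testing.

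**Step 2: does the stated analysis separate them?** Table 3 puts no symptom condition on the positive-versus-negative comparison. The model description names correlation and no confounder.

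**Step 3: how large could the effect be?** Suppose the result has no effect on behaviour. Then

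apparent difference = (symptomatic share of positive tests − symptomatic share of negative tests) × (extra adherence due to symptoms).

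All inputs are assumptions, because the article gives none of them: adherence 50% without and 80% with symptoms (30 points extra), and 3% of negative tests symptomatic. Adherence after a negative is then 0.97 × 50 + 0.03 × 80 = 50.9%.

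| Symptomatic share of positives (assumed) | Adherence after a positive | Apparent difference |
|---|---|---|
| 20% | 0.8 × 50 + 0.2 × 80 = 56% | 5.1 points |
| 40% | 0.6 × 50 + 0.4 × 80 = 62% | 11.1 points |
| 60% | 0.4 × 50 + 0.6 × 80 = 68% | 17.1 points |

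Within each symptom stratum the difference is zero by construction (50 versus 50, 80 versus 80), so stratifying removes the artefact in this example.

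A wider assumed range takes symptomatic shares of 30–70% in positives and 2–10% in negatives, with 10–40 points extra adherence. The smallest value is (0.30 − 0.10) × 10 = 2.0 points, a middle case is (0.50 − 0.05) × 30 = 13.5, and the largest is (0.70 − 0.02) × 40 = 27.2. A larger sample changes none of these.

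**The case against.** The strongest reply is that this is a journal article. It lists no covariates for the substudy model, does not say the model is unadjusted, and an analysis plan not shown may adjust for symptoms. The symptom data are collected, the analysis is called primarily descriptive, and one of the two wordings of the hypothesis claims association only. Much of this stands: a missing covariate list alone would be no finding. What remains is that the article does fix the primary contrast, fixes it without a symptom condition, and attaches a causal hypothesis to it. The multivariable modeling mentioned in the substudy's sample-size section does not settle this, because it concerns the link between frequent testing and community disease burden.

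A reader might draw stronger conclusions that the documents do not support:
- That symptomatic people are told to stay in the schedule. The text under Fig. 6 may only rule out symptom-triggered home tests, with the asymptomatic condition still governing.
- That Table 3 allows stratification by demographics and nothing else. The demographic strata attach to the overall proportion; the positive-versus-negative comparison follows with no strata named.
- That the substudy sets out to estimate the effect of a result in people unaware of infection. No such aim is stated.
- That the untracked deviations make the problem irreparable. Symptoms are asked about separately.

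**Conclusion.** The point holds as a limit on interpretation that can be repaired with planned data. As described, the crude contrast mixes the result with symptoms and cannot bear the causal wording in the substudy's Data analysis plan. This rests on two things: that some tests are taken with symptoms, which is inferred from the testing instructions, and that symptoms both raise the chance of a positive and change behaviour, which is a general expectation and not a figure in the article.

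The size is unknown. The 5 to 17 points, and the wider 2 to 27, show the mechanism under assumed inputs and should not be read as estimates for this study. Nor does it follow that the primary comparison must be confined to symptom-free tests. That is one defensible choice, but it gives up positive results; a stratified and adjusted comparison meets the concern without it. The point deserves action but does not put the substudy in doubt.

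**What to change.** 1. Present the positive-versus-negative comparison of adherence stratified by symptom status at the time of the test.
2. Enter that status in the mixed model as a time-varying covariate.
3. Align the hypothesis in the substudy's Data analysis plan with the association wording in its Outcomes and measures section.
4. Reconcile the instruction to test asymptomatic people with the text on symptoms under Fig. 6, so that it is clear which tests the comparison contains.

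No new data collection or change of sample size is needed. It should be confirmed against the schedule of events (Additional file 3, not shown here) that symptom items can be dated to each test.

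The cost is precision. As an illustration with assumed counts, 50% adherence and one independent observation for each of 5000 participants, 100 positives give a 95% half-width of 1.96 × √(0.25/100 + 0.25/4900) = 9.9 points for the difference. With 50 positives it is 1.96 × √(0.25/50 + 0.25/4950) = 13.9 points, and wider still in a stratum with few negatives. Symptoms that begin after the test but within the questionnaire week are not covered and should be named as a remaining limitation.
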